### Program assessment and treatment fidelity/process evaluation

#### Training and supervision

To promote high fidelity in intervention delivery, a 3-day training course has been developed to ensure intervention delivery according to protocol. The 3-day course is designed as an interactive training consisting of a range of lectures combined with practical training exercises, group reflection and discussions, and individual reading assignments. The training will give an in-depth introduction in guided self-determination, supported conversations for adults with aphasia, and cover all the theoretical underpinnings of the intervention (Table 3). The participants are provided with relevant research articles, books, and book chapters that provide updated knowledge on psychosocial issues following stroke, outline the theoretical underpinnings of the intervention, and provide guidance in the approaches chosen for the intervention.

**Table 3 Tab3:** Overview of components of the 3-day training course

Main component	Lecture topic	Type of training
Understanding stroke survivor’s every-day challenges	Living with stroke	Educational video, group discussion
Theoretical underpinnings of the intervention	Introduction to the intervention’s essential ideas and philosophy underpinning the intervention	Lecture
	Psychosocial issues following stroke	Lecture
	Understanding challenges and changes for work-aged stroke survivors	Lecture
	Bodily changes following stroke	Lecture
	Gendered perspectives on stroke	Lecture
	Aphasia and living life with language impediments	Lecture
	The aphasic storyteller	Lecture
	Supported conversations for adults with aphasia	Lecture
	When things become incomprehensible: Cognitive and other invisible changes following stroke	Lecture
	Ethical considerations in the role as guide	Lecture
	Guided self-determination and the role as guide using the intervention’s metaphor	Lecture
Guided self-determination	Presentation of the intervention’s work sheets	Lecture
	Presentation of the intervention’s work sheets	Practical exercise, roleplay, group discussion
Supported conversation for adults with aphasia	Supported conversations for adults with aphasia	Practical exercise
	Using the work sheets and different approaches to communication	Lecture, practical exercise
Documentation	Using log notes	Lecture, group discussion
General discussion and reflection	Throughout the program	Group discussion

Health care professionals with knowledge and experience in working with stroke patients,

primarily nurses and occupational therapists, complete the 3-day training course to be certified to deliver the intervention. Intervention personnel writes a log, using a standardized format, to document how each session in the intervention is conducted, any problems encountered and how they deal with these. In addition, group supervising seminars for the intervention personnel are arranged throughout the study period. The seminars are led by members of the research team. These seminars provide an arena for exchange of experiences between intervention personnel and between intervention personnel and the research team. The purpose is to discuss any difficulties in the intervention encounters and support the intervention staff in implementing the intervention according to protocol. Sharing of experiences through storytelling and group reflection and discussions are the main mode of communication in the seminars. The seminars are an arena for guidance and supervision for the intervention personnel, and it allows the research team to uncover potential needs for reinforcement of training to promote intervention fidelity. Individual supervision is provided as needed between group supervision seminars.

Data collectors with a health care background (RN or OT) collect data for the study. They receive a written data collection procedure training protocol and individual training in administering each of the outcome measures. The data collectors are supervised to ensure that data is collected in a consistent manner throughout the study.

#### Process evaluation

The process evaluation of this study is guided by the process evaluation framework outlined by the MRC Population Health Sciences Research Network (PHSRN) [72]. As part of this evaluation, 15–20 participants from the intervention and control groups are invited to participate in individual qualitative interviews after study completion (12 months post stroke). The purpose of these interviews is to gain an in-depth understanding of the participants’ experiences with the adjustment process following the stroke, and their experiences with participating in the intervention or control group and assessment interviews. The interview approach is based on Ricoeur’s phenomenological hermeneutics [73] and the data will be analyzed according to Ricoeur’s interpretation theory [74].

Post-intervention focus groups will be conducted with intervention personnel following the completion of all intervention programs. The purpose of the focus groups is to ascertain an in-depth understanding of the intervention personnel’s experiences with delivering the intervention, their impression of participant responsiveness to the intervention, and to uncover potential threats and facilitators to implementation adherence fidelity.

Focus group interviews with data collectors conducting the data collection interviews will be conducted following completion of all data collection. The purpose of the focus group interviews will be to gain an in-depth understanding of the data collection interviews from the data collectors’ perspective and to assess the suitability of the chosen outcome measures. Thematic content analysis will be applied to the focus group interview data [75].

Detailed enrolment records, attrition protocol, and intervention protocols are logged to facilitate quantitative analysis of implementation fidelity and intervention adherence [76, 77]. Descriptive statistical analyses will be applied to the quantitative data with the purpose of describing the study’s implementation adherence. Furthermore, quantitative data from these protocols will be used to construct an independent variable of intervention adherence (fidelity) to be included in the outcome analyses of the study.

The attrition rate is expected to vary between the intervention and control groups due to the relative extensiveness of the intervention. We will attempt to identify key predictors of attrition status (i. e baseline stroke severity and demographic characteristics). The attrition protocol will be analyzed to inform the process evaluation with regards to possible adjustments in future studies.

## Discussion

A stroke may create a number of burdensome psychosocial difficulties and many stroke survivors report unmet support needs, particularly upon discharge from the specialized stroke care in the hospital [1–5]. Nevertheless, few effective interventions aimed at promoting coping and psychosocial well-being exist to support the stroke survivor, and their family, once they return to the community. Therefore, conducting well designed intervention studies are needed In this study, we test the effectiveness of a theoretically and empirically informed intervention, developed within the framework of complex interventions proposed by the UK medical research council [39]. Thorough feasibility testing prior to the trial, have helped inform the current trial [41–43] and improved the methodology as well as the intervention itself.

A major strength in this study is the combination of classical RCT methodology with a thorough process evaluation to enable us to evaluate the implementation fidelity and intervention adherence and be better equipped to interpret our findings. Furthermore, by recruiting participants from 11 hospitals and include close to thirty trained intervention staff to deliver the intervention, our trial will mirror the “real world” of stroke follow up care with its inherent variability in terms of both acute and rehabilitation services provided. This will strengthen the trials’ external validity. Because the intervention may be delivered by community-based nurses, and other health care professionals with limited additional training, the intervention will be easier to implement in community care, should it prove effective.

Despite the careful planning and feasibility testing before commencing the trial, there are a number of risks as well. These include the dependency of a large number of clinical staff and hospitals managers at a number of hospitals to ensure consistent recruitment and a great number of intervention staff, which may introduce variability in the delivery of the intervention. Furthermore, many researchers and research assistants are involved in data collection, which again may introduce inconsistency in data collection. To address these risks, we have developed a strong team of researchers with regular meetings, stringent protocols to ensure consistency, through training and supervision of all involved and two designated study coordinators responsible for one geographical area each. One designated project leader and a multidisciplinary team of senior researchers experienced in conducting trials will also monitor the trial to ensure that the study protocol is followed and/or address any problems that we might encounter.

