### Sample size calculations

The study’s sample size was calculated based on the primary outcome measure GHQ-28, which has been used in a comparable trial [31, 32]. Following Watkins et al.’s results, we deemed an odds ratio of 1.6 or higher between-groups (intervention/control) with normal mood after 6 and 12 months to be clinically relevant. The calculations are based on a repeated measures logistic regression model for the output variable “normal mood” (GHQ-28 < 5) with two measurements for each patient (i.e. one at 6 months and one at 12 months), with one binary input variable specifying group allocation. Based on 80% power across both time points, the calculated sample size of this study is 300 participants, 150 in each arm of the study. To allow for a 10% dropout rate, we have inflated the number to 330 participants in total.

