### Statistical analysis

Data analysis will be conducted as intention-to-treat. Missing data will be imputed using multiple imputation technique [71]. All analyses will be performed using statistical software such as IBM SPSS or R. For group comparisons of individual variables, categorical variables will be analyzed using chi-squared tests, and continuous variables will be analyzed using t-tests or Mann-Whitney U tests (for two-group comparisons) and F-tests or Kruskal-Wallis tests (for more than 2 groups). The primary statistical analysis will be a repeated measures logistic regression model for the dichotomized output variable “normal mood yes/no” (GHQ-28 < 5 versus GHQ-28 ≥ 5) with two measurements for each patient (i.e. one at 6 months and one at 12 months), with one binary input variable specifying group allocation. Independent variables will include demographic variables, stroke type and severity measurements, rehabilitation service use and relevant medical variables. Medical and demographic variables will be included in the data analysis model to control for group differences at baseline. Secondary analyses, e.g. sub-group analyses, will be conducted with primary, secondary and process outcomes. The psychometric properties of GHQ-28 will be examined to confirm stability of dimensions in a Norwegian general stroke population across time points. All statistical tests will be performed as two-sided tests with a significance level of 0.05.

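### With close to thirty providers in the intervention arm only, the stated primary model and sample size make no allowance for provider clustering; if the provider ICC is positive, the standard error is understated

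*Protocol article*

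**What the plan says.** **Delivery.** The section on the intervention describes eight individual sessions between the patient and a trained nurse or occupational therapist. The Discussion counts it as a strength that the trial will "include close to thirty trained intervention staff to deliver the intervention". It then lists among the risks "a great number of intervention staff, which may introduce variability in the delivery of the intervention", to be met by training, supervision, protocols and monitoring. Under Control group, controls receive usual care and have no such provider.

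**Analysis.** The Statistical analysis section states: "The primary statistical analysis will be a repeated measures logistic regression model for the dichotomized output variable". The model has two measurements per patient, at 6 and 12 months, "with one binary input variable specifying group allocation". The further covariates are demographic, stroke-related, medical and service-use variables. Neither provider nor centre is named, although Randomization and blinding stratifies by centre. On significance: "All statistical tests will be performed as two-sided tests with a significance level of 0.05".

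**Sample size.** The calculation uses the same model. On the target effect: "we deemed an odds ratio of 1.6 or higher between-groups". On the result: "Based on 80% power across both time points, the calculated sample size of this study is 300 participants", with 150 per arm. On attrition: "To allow for a 10% dropout rate, we have inflated the number to 330 participants in total". No design effect appears.

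**Fidelity.** Process evaluation plans a variable for adherence to the intervention, built from the study's records, to enter the outcome analyses.

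**The concern.** This is a partially nested design: patients are grouped by provider in one arm and ungrouped in the other. The intervention is a conversation that follows the patient's lead and may depart from the topical outline, so it is plausible that some providers achieve more than others. Patients of the same provider would then have correlated outcomes. A model whose only named correlation is between two measurements of one patient counts those patients as independent information.

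At stake are the width of the confidence interval for the primary odds ratio, the real significance level of the primary test, and the power claimed for 300 patients. The article itself expects variability between staff, so the matter arises from its own account of the trial.

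**Working it through.** **Inputs from the article.** Two-sided alpha 0.05; power 80%; odds ratio 1.6; 300 analysable patients (150 per arm); 330 enrolled (300 x 1.10, so 165 per arm); close to 30 providers.

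**Inputs assumed.** Provider ICC of 0.01, 0.05 or 0.10, and equal caseloads at first. The article gives neither. The ICC is taken for one summary outcome per patient.

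**Step 1: the plan's own figure.** The total for two equally correlated measurements is

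N = 2(1.960 + 0.842)^2 [1/(p0 q0) + 1/(p1 q1)] / (ln 1.6)^2 x (1 + r)/2,

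where p0 and p1 are the control and intervention proportions with normal mood, q = 1 - p, and r is the within-patient correlation. The article states neither p0 nor r, so 300 cannot be fully checked. For p0 from 0.30 to 0.60, N is about 288 to 319 at r = 0 and about 432 to 479 at r = 0.5. The steps below therefore start from the article's stated 80% at 300 and show only what provider clustering would change.

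**Step 2: caseload.** 150/30 = 5.0 analysable and 165/30 = 5.5 enrolled patients per provider (m).

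**Step 3: variance.** The design effect in the intervention arm is DE = 1 + (m - 1) x ICC. With equal arms and clustering in one, the variance of the treatment contrast is multiplied by V = (1 + DE)/2 and the standard error by sqrt(V).

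Example, m = 5.0 and ICC 0.05: DE = 1 + 4 x 0.05 = 1.20; V = 2.20/2 = 1.10; sqrt(V) = 1.049.

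**Step 4: consequences.**
- Type I error of a test that uses the understated standard error: 2 x [1 - Phi(1.96/sqrt(V))].
- Power of a test that uses the correct standard error: Phi(2.80/sqrt(V) - 1.96).
- Analysable N needed to restore 80%: 300 x V.

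| ICC (assumed) | DE, m = 5.0 / 5.5 | V | SE ratio | Type I error | Power | N |
|---|---|---|---|---|---|---|
| 0.01 | 1.040 / 1.045 | 1.020 / 1.022 | 1.010 / 1.011 | 5.2% / 5.3% | 79.2% / 79.1% | 306 / 307 |
| 0.05 | 1.200 / 1.225 | 1.100 / 1.113 | 1.049 / 1.055 | 6.2% / 6.3% | 76.2% / 75.7% | 330 / 334 |
| 0.10 | 1.400 / 1.450 | 1.200 / 1.225 | 1.095 / 1.107 | 7.4% / 7.7% | 72.5% / 71.6% | 360 / 368 |

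**Step 5: uneven caseloads.** Replacing m by m(1 + CV^2), with an assumed coefficient of variation of 0.6, gives SE ratios of 1.07 to 1.08 at ICC 0.05 and 1.14 to 1.15 at ICC 0.10.

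**The case against.** Several objections carry weight.

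- **Silence is not a statement of independence.** The article does not say whether the model is marginal or has random effects, nor which variance estimator is used, and an analysis plan not shown may add a provider term. That is fair. Still, the article does fix the outcome, the repeated-measures structure, the group term and the types of covariate, and it sizes the trial on that model. The point is about the model as stated.
- **The article does more than train and supervise.** A reader of the Discussion might infer that delivery variability has no analytic answer at all. The planned fidelity variable shows otherwise. It is, however, a covariate for adherence and leaves the correlation among patients of one provider unmodelled.
- **The type I figures need a particular null.** If the intervention does nothing for anyone, providers cannot induce correlation. The figures apply only where provider effects vary around an average of zero. This stands.
- **Centre works the other way.** Stratifying by centre and then omitting centre tends to make the standard error too large. The size of this offset cannot be derived from the article, so a flat statement that the intervals are too narrow goes further than the document allows.
- **Caseload and correlation are inferred.** About 5 per provider is an average, and the article does not say that one provider gives a patient all eight sessions. The 12-month measurement falls six months after the intervention ends, so provider correlation may differ between the two time points.
- **Generalisation.** A reader might infer that the article claims its result for community staff at large. The Discussion says only that implementation would be easier if the intervention works, which is a conditional remark on feasibility.

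**Conclusion.** The point holds in conditional form. The article's own counts imply a partially nested design, and the model and sample size it states make no allowance for provider. Any positive provider ICC, taken alone, makes the standard error from that model too small. The shortfall is negligible at an ICC of 0.01 and modest at 0.05 to 0.10, where the correct standard error is about 5% to 11% larger with equal caseloads. Power falls by about 1, 4 and 8 percentage points at 0.01, 0.05 and 0.10. At 0.05, restoring 80% needs 330 to 334 analysable patients, which uses up the whole dropout allowance.

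These sizes rest on an assumed ICC, an average caseload and one summary outcome per patient; the type I figures also need variation around a zero mean effect. The net direction, once the omitted centre factor is counted, is not established. The primary analysis is worth changing, but the article does not show that its intervals will in fact be too narrow.

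**What to change.** Specify the primary model as partially nested, by one of two routes:

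- a provider random effect that acts in the intervention arm only, alongside the within-patient correlation; or
- a marginal model with variance clustered by provider in the intervention arm, each control patient as a cluster of one, and a small-sample correction suited to about thirty providers.

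Choose the route before the data are analysed, since the first gives an odds ratio conditional on provider and the second a population-averaged one. Include centre, as the stratification factor, in either. State a rule for patients seen by more than one provider. Report the provider ICC and the caseload distribution, and give the power statement with an assumed ICC.

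The cost is small. The standardised logs that intervention personnel write for each session should supply provider identity, and the design does not change. The interval will be slightly wider if the ICC is positive. If the ICC is near zero, the provider variance may be estimated unstably; the provider part then drops out and the planned structure remains.

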### Trial status

Patient recruitment to the trial has ended, but recruitment to the process evaluation is ongoing at the time of manuscript submission. Data collection will continue to the end of June 2018.
